### Follow-up assessments

Patients are appointed outpatient visits as part of the clinical investigation at 3, 6, and 12 months postoperatively. For study purposes, except quality of life measurements, patients do not undergo any diagnostic or other procedure not belonging to the common repertoire of assessments carried out after ACL repair. Specifically, we avoid invasive procedures, blood sampling, or imaging tests exposing subjects to radiation or contrast agents. The investigators consider the possible burden caused by extra clinical tests negligible.

We assess the following items at the scheduled visits:

#### Three months postoperatively

- Physical examination, including circumferential measurement of both legs at defined landmarks, Lachman and pivot shift tests, KT-1000 arthrometer objectifying of instability, one-legged hop test, Lysholm, Tegner, and IKDC scores, knee and kneeling pain measured by visual analogue scales

- Any complications or complaints raised by the patient, GP/ ambulatory surgeon, or Clinical Investigators

- Resumption of work

- MRI scan according to local standards

#### Six months postoperatively

- Physical examination, including circumferential measurement of both legs at defined landmarks, Lachman and pivot shift tests, KT-1000 arthrometer objectifying of instability, one-legged hop test, Lysholm, Tegner, and IKDC scores, knee and kneeling pain measured by visual analogue scales

- Any complications or complaints raised by the patient, GP/ ambulatory surgeon, or Clinical Investigators

- Resumption of work and leisure activities

- MRI scan according to local standards

Patients and Investigators responsible for follow-up examinations may learn about the assigned treatment after completing the six-month CRF.

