**Design/ Methods:**

SPOT is a randomised, controlled, patient and investigator blinded trial conducted at a single academic institution. Eligible patients are scheduled to arthroscopic ACL repair with triple-stranded hamstring grafts, conducted by a single, experienced surgeon. Intraoperatively, subjects willing to engage in this study will be randomised to transplant tethering with either resorbable screws or resorbable pins. No other changes apply to locally established treatment protocols. Patients and clinical investigators will remain blinded to the assigned fixation method until the six-month follow-up examination.

The primary outcome is the side-to-side (repaired to healthy knee) difference in anterior translation as measured by the KT-1000 arthrometer at a defined load (89 N) six months after surgery. A sample size of 54 patients will yield a power of 80% to detect a difference of 1.0 mm ± standard deviation 1.2 mm at a two-sided alpha of 5% with a t-test for independent samples.

Secondary outcomes (generic and disease-specific measures of quality of life, magnetic resonance imaging morphology of transplants and devices) will be handled in an exploratory fashion.

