### Primary endpoint

We pose the primary hypothesis that the RigidFix^® ^system preserves graft tension gained during surgery, and leads to lower KT-1000 arthrometer side-to-side differences than the BioCryl^® ^screw after six months of follow-up.

Specifically, we will test the hypothesis that RigidFix^® ^decreases the average difference gained with interference screws by 1.0 ± standard deviation 1.2 mm. The investigators consider this difference clinically sound, important, and measurable by KT-1000 arthrometer testing. Twenty-four subjects a treatment arm will allow for detecting this difference with an 80% chance at a two-sided alpha-level of 5%. Assuming a drop-out rate of 10%, 54 patients will be enrolled in this study.

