### Design

SPOT is a patient and investigator blinded, randomised controlled trial conducted at a single academic institution.

Randomisation is carried out in the operating theatre shortly before transplant fixation, with random codes drawn from sealed envelopes. We use block-randomisation with five subjects a block following a computer-generated random list [19].

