### Ethical considerations

This protocol and all accompanying documents were approved by the local Institutional Review Board (IRB).

According to IRB recommendations and requirements, information leaflets explicitly note that "a benefit from participation in this trial cannot be guaranteed."

We will stress the principle of randomisation as "treatment assignment by chance, without the possibility of the investigator, other health care professionals involved in this study, or the patient influencing the choice of treatment." We also tell patients that, as long as they keep agreement in participation, they will not know their assigned treatment until the six-month follow-up visit.

We will notify the IRB of any significant changes to the protocol. Also, we will notify the IRB within ten working days of the discovery of any severe adverse events which occur during this investigation.

Confidentiality of subject data will always be maintained. Subject anonymity will be guaranteed and all documentation about a subject (including radiographs) will be kept in secure location.

This investigation strictly adheres to the relevant articles of the Declaration of Helsinki as adopted by the 18^th ^World Medical Assembly in 1964 and its later revisions, as well as to principles of GCP, developed within the Expert Working Group (Efficacy) of the International Conference on Harmonisation of Technical Requirements for Registration of Pharmaceuticals for Human Use (ICH).

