### Surgery and rehabilitation

All devices and instrumentations used in this clinical investigation bear the CE mark. They belong to the regular implants used for ACL repair at the study hospital since 2002. Except different graft anchoring, similar treatments apply to patients in both study groups. All participants undergo internationally accepted surgically procedures by a single surgeon ([name]) with extensive experience in ACL repair using both the BioCryl^® ^screw and RigidFix^® ^cross pins. Also, postoperative care and rehabilitation programs do not differ from those employed outside a clinical trial.

All repairs are carried out under general anaesthesia, with the patient in a supine position. Perioperative antibiotic prophylaxis comprises 2 g of cefotiam. Patients receive 40 mg of enoxaparin daily for prophylaxis of thromboembolic events until full weight bearing.

The knee joint is accessed through two to three standard portals. Meniscal injuries are addressed with partial resection or repair.

Hamstring tendons are harvested via a small incision over the insertion of the pes anserinus at the anterior medial tibia by a closed tendon stripper, and prepared as triple-stranded grafts.

Tibial and femoral tunnels are drilled to approximate graft thickness (usually 8 to 9 mm) with the use of a guiding wire. Grafts are fixed with the knee in 30° flexion to achieve firm tension.

Postoperatively, the knee is stabilized for three days by a zero-degree splint. Afterwards, flexion is limited to 90° by a Secutec^® ^orthosis for six weeks. Patients are allowed partial weight bearing with walking crutches. Subjects are prescribed intense physical therapy for motion exercise, and to strengthen thigh muscles. Normally, full range of motion and weight bearing is achieved until week 12 after surgery.

Patients in the experimental group have their grafts secured by tibial and femoral RigidFix^® ^pinning. Patient in the control group receive tibial and femoral BioCryl^® ^screws.

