### Physical examination

Before physical examination, both knees are prepared by applying opaque dressings to hide scars and to blind the examining doctors for the managed side.

Examination is performed independently by two of three board-certified surgeons ([name], [name], [name]) who had not operated on any of the patients in the study. The responsible surgeon ([name]) conducts a third clinical examination after completion of the case report forms. We document his examination findings separately and consider them as the diagnostic reference standard. We assess both interobserver agreement by kappa statistics and the accuracy of measurements taken by independent observers comparing with those of the responsible surgeon.

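### Examiners may learn each patient's arm after that patient's six-month visit, while the same pool of surgeons is still taking later patients' primary KT-1000 readings

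*Protocol article*

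**What the plan says.** The release rule closes the six-month visit list (Protocol article, Six months postoperatively): "Patients and Investigators responsible for follow-up examinations may learn about the assigned treatment after completing the six-month CRF". Two other places end blinding at the same moment. The abstract (Design/ Methods) says "Patients and clinical investigators will remain blinded to the assigned fixation method until the six-month follow-up examination", and Ethical considerations reports that patients are told "they will not know their assigned treatment until the six-month follow-up visit". All three read naturally as applying to each patient's own visit.

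The primary outcome is the side-to-side KT-1000 difference at six months. The six-month list puts "KT-1000 arthrometer objectifying of instability" inside the physical examination, and the section Physical examination states "Examination is performed independently by two of three board-certified surgeons". The same section has opaque dressings put on both knees, so that examiners cannot see which side was operated on.

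On allocation, the section Design states "We use block-randomisation with five subjects a block following a computer-generated random list". It does not give the split between arms within a block. Surgery and rehabilitation states "All participants undergo internationally accepted surgically procedures by a single surgeon".

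**The concern.** One surgeon operates on all 54 patients, so surgery dates, and with them the six-month visits, are spread over time. The accrual period is not given. Release follows each patient's CRF, yet the pool of examiners serves the whole trial. When a late patient of a block attends, the examiners may already have been told the arms of earlier patients in that block. They may also have been able to set those patients' laxity readings against their arms.

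Two things follow. Released codes carry information about the next allocations in a block of known size. A running comparison of pins and screws can also form expectations in examiners who still have primary readings to take. The operating surgeon necessarily knows the device, so the blinding of the independent examiners is the main protection of this endpoint. What is at stake is the credibility of the single confirmatory comparison.

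**Working it through.** **The plan's own figure.** Inputs from Primary endpoint: difference 1.0 mm, SD 1.2 mm, two-sided alpha 5%, power 80%, drop-out 10%. The t-test has power 0.789 with 23 per arm and 0.807 with 24, so 24 per arm is right. Inflation: 48 / 0.9 = 53.3, rounded up to 54. The sample size reproduces, and this point does not touch it.

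**Inputs for the blinding check.** From the documents: block size five, 54 patients (ten full blocks and four patients of an eleventh), release after each six-month CRF. Assumed, because the documents are silent:
- each block is 3:2 or 2:3 at random, so the 10 + 10 = 20 possible orderings are equally likely;
- examiners know the randomisation order and the block boundaries;
- visits follow surgery order;
- every earlier code in the block is known before the next reading.

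**Forced allocations.** No arm can occur more than three times in a block. A patient's arm is therefore certain exactly when three earlier block-mates are known to share an arm.
- Positions 1 to 3: never.
- Position 4: the first three are alike in 2 of 20 orderings, 0.1.
- Position 5: the first four split 3:1 in 8 of 20 orderings, 0.4.

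Sum per block: 0.1 + 0.4 = 0.5. Over the trial: 10 × 0.5 + 0.1 = 5.1, and 5.1 / 54 = 9.4%.

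**Best guess.** The chance that the likelier arm is correct, by position, is 0.5, 0.6, 0.6, 0.7, 0.7. The mean is 3.1 / 5 = 62%, against 50% with no codes released.

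**Weaker assumptions.**
- Codes lag by one patient: at position 5 only three codes are known, and these are alike in 2 of 20 orderings. That is 0.1 per block, 10 × 0.1 = 1.0 of 54 (2%).
- Codes lag by two patients or more: three codes are never known in time, so 0.
- An examiner knows only the codes of patients he examined (two-thirds of them, taken as independent): 5.1 × (2/3)³ = 5.1 × 0.296 = 1.5 of 54.

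**Scale, for illustration only.** Suppose 10% of readings are forced and the arm contrast in those readings is shifted by 1.0 mm. The bias is 0.10 × 1.0 = 0.10 mm. With 24 per arm and SD 1.2 mm, the two-sided type I error becomes about 5.9% instead of 5%. The 1.0 mm shift is an assumption, and the effect of uncertain guesses is not counted.

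**After the change.** With no codes released to examiners before the last primary reading, released codes force 0 of 54 allocations; 54 patients and about 80% power remain.

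**The case against.** The case against rests on likelihood, and much of it stands.

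- The rule says examiners may learn the arm, not that they will. Envelopes are drawn in theatre, the examiners did not operate, and no sentence gives them the sequence or block boundaries. The figure of 5 is therefore a ceiling.
- Two of the three surgeons examine each patient, so no single examiner handles every CRF. Codes could still be shared.
- The dressings matter more than they first appear to. The endpoint is a signed difference between knees, so an examiner who guesses the arm but not the operated side has less means to steer it. Laxity may itself reveal the side, so the protection is partial.
- The running comparison is not an independent source of bias. Expectations about pins and screws distort a later reading differentially only if that patient's arm is known or guessed.
- Holding codes until each patient's own 12-month visit would close most of the deduction route. Block-mates would already have their six-month readings unless a block took over six months to fill, which for 54 patients means 54 / 5 × 6 = 65 months of accrual. The protocol as written does not do this either.

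None of these points removes the permission in the text.

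A reader might infer a larger problem: with every block 3:2 in the same direction, 1.5 allocations per block are forced, about 16 of 54, and the best guess is right 72% of the time. The documents do not support this. Such a list gives about 32 against 22 patients, and 22 × 0.9 = 19.8 evaluable falls short of the planned 24. The blinded baseline would also be 60%, not 50%, because always guessing the larger arm is right three times in five. A list alternating 3:2 and 2:3 would balance the arms, but nothing describes one or suggests that examiners would know the pattern.

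**Conclusion.** The point holds as a modest weakness in the release rule. The protocol article lets examiners learn earlier patients' arms while primary readings are still being taken, and nothing in it delays release until the last one. With a random mix of 3:2 and 2:3 blocks, the exposure is at most about 5 of 54 forced allocations and a 62% best guess against 50%. It falls to about 1 of 54 with a one-patient lag and to none with longer lags. The ceiling needs all the assumptions listed in the check. It also takes the KT-1000 reading to be made by the examining surgeons, as its place in the visit list implies.

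A reader might go further and infer that the primary result is biased or that blinding failed. The documents do not show that. They show a permitted exposure, partly offset by the dressings. The change is worth making because it costs little and protects the only confirmatory endpoint.

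**What to change.** Amend the closing sentence of Six months postoperatively, and the matching blinding sentence in the abstract, to say that no follow-up examiner receives any patient's allocation until the six-month CRF of the last randomised patient is completed and locked.

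The information given to patients under Ethical considerations can stay. Patients may still be told at month six, by someone other than the three examiners, with a request not to disclose it to them.

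Cost: two sentences in the protocol, a later date at which examiners learn allocations, and another person to inform patients. A patient may still let the arm slip at a later visit, so some leakage remains possible. Sample size, power and analysis are unchanged.

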#### Twelve months postoperatively

- Physical examination, including circumferential measurement of both legs at defined landmarks, Lachman and pivot shift tests, KT-1000 arthrometer objectifying of instability, one-legged hop test, Lysholm, Tegner, and IKDC scores, knee and kneeling pain measured by visual analogue scales

- Any complications or complaints raised by the patient, GP/ ambulatory surgeon, or Clinical Investigators

- Resumption of work and leisure activities

- MRI scan according to local standards

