## Discussion

After ACL repair, most patients rarely recognize slightly weakened anterior knee stability in everyday life. However, subjects with a high recreational and sporting activity and physically strenuous professions often suffer from recurrent events of giving-way, especially on hastened movements. This poses a high risk for secondary knee injury. Of note, muscular training cannot compensate for residual laxity, outbalancing the anticipated benefit from surgical repair.

Thus, attempts to optimize the surgical technique may be valuable. Currently, surgeons performing ACL reconstruction use screws, pins, buttons, and cramps for graft fixation because of individual preference, or institutional orders. The latter are chiefly driven by cost considerations. For example, the purchase price of a RigidFix^® ^tray is ten times higher than that of BioCryl^® ^screws. Obviously, the more expensive implant must prove a distinct *clinical *advantage over the common one to justify its further use. Unfortunately, there is lack of robust evidence on the effectiveness of either fixation method beyond laboratory and animal experiments.

Although conceptually impressive, there is no comparative study that proved a clinically measurable advantage of RigidFix^® ^over screws. The investigators consider the equipoise principle fulfilled, since it is unclear whether screw or pins lead to better long-term stability, or show any measurable differences at all. We hope that the results from this pragmatic study can clarify this issue.

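### Follow-up examiners may be told the allocation after the six-month CRF, so the exploratory 12-month laxity readings may be taken unblinded, and no reason is given

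*Protocol article*

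**What the plan says.** The limit on blinding appears in three places in the protocol article, and they agree.

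- Abstract, Design/Methods: "Patients and clinical investigators will remain blinded to the assigned fixation method until the six-month follow-up examination".
- Ethical considerations: patients are told that "they will not know their assigned treatment until the six-month follow-up visit".
- Six months postoperatively: "Patients and Investigators responsible for follow-up examinations may learn about the assigned treatment after completing the six-month CRF".

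Follow-up assessments sets the schedule: "Patients are appointed outpatient visits as part of the clinical investigation at 3, 6, and 12 months postoperatively". Month 12 is thus the only visit after the permission takes effect. Its list of examinations matches the six-month list and includes "Lachman and pivot shift tests, KT-1000 arthrometer objectifying of instability, one-legged hop test, Lysholm, Tegner, and IKDC scores".

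The primary hypothesis is tied to the earlier visit, namely that pinning "leads to lower KT-1000 arthrometer side-to-side differences than the BioCryl^® ^screw after six months of follow-up". Secondary endpoints and Statistical analysis both restrict confirmatory testing to that hypothesis and treat everything else as exploratory.

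Physical examination describes the masking. Opaque dressings on both knees conceal from the examiners which knee was operated on. Two of three surgeons who did not operate on study patients examine independently.

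**The concern.** Lachman and pivot shift are manual tests. KT-1000 uses a defined load but is still read by an operator. The protocol itself treats the physical examination as observer-dependent, since it plans kappa statistics and a comparison with the operating surgeon. The direction in which an informed examiner might lean is also clear, because the stated hypothesis is that pins give less laxity than screws.

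Examiners do not need the allocation to carry out the 12-month examination, and the article gives no reason for releasing it to them. The promise in Ethical considerations concerns when patients learn their treatment, and it requires nothing for examiners.

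At stake is how the 12-month laxity results can be read. If examiners have been told, a difference between arms at 12 months, or the fading of a six-month difference, could not be cleanly separated from examiner expectation. A comparison of month 6 with month 12 would set blinded readings beside possibly unblinded ones.

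**Working it through.** **Step 1: set the provisions side by side.**

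| Question | Protocol article | Section |
|---|---|---|
| Until when are examiners blinded? | Six-month examination | Abstract; Six months postoperatively |
| Is later unblinding required or permitted? | Permitted | Six months postoperatively |
| Is there an examination afterwards? | Yes, at 12 months only | Follow-up assessments |
| Are the laxity tests repeated there? | Yes: KT-1000, Lachman, pivot shift | Twelve months postoperatively |
| What do the dressings conceal? | Scars and the operated side, not the device | Physical examination |
| Is a reason for unblinding examiners given? | None | – |

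The gap follows from these provisions without any calculation. The arithmetic below only shows what size of bias would matter.

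**Step 2: reproduce the plan's own figure.** Inputs from Primary endpoint: difference 1.0 mm, SD 1.2 mm, two-sided alpha 5%, power 80%, drop-out 10%. The standardised difference is 1.0/1.2 = 0.833. The exact t-test calculation gives 23.6, rounded up to 24 per arm, with power 80.7% at 24. Allowing for drop-out, 48/0.90 = 53.3, or 54 when rounded up. The plan's 24 per arm and 54 enrolled are confirmed.

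**Step 3: illustrate the effect of examiner bias at 12 months.** Assumptions: no true difference, 24 evaluable per arm, SD 1.2 mm as planned for month 6, a uniform shift *b* between the arms, and a two-sided 5% t-test.

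- Standard error of the difference: 1.2 × √(2/24) = 0.346 mm.
- Degrees of freedom: 2 × 24 − 2 = 46; critical value 2.013.
- Noncentrality: *b*/0.346.
- Probability of nominal p<0.05: P(|T| > 2.013), with T noncentral t on 46 degrees of freedom.

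| Assumed shift *b* | Noncentrality | P(nominal p<0.05) |
|---|---|---|
| 0 mm | 0 | 5.0% |
| 0.1 mm | 0.289 | 5.9% |
| 0.3 mm | 0.866 | 13.6% |
| 0.5 mm | 1.443 | 29.3% |

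These shifts are 10%, 30% and 50% of the 1.0 mm target difference. None comes from the documents.

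**The case against.** There is a serious case for leaving the text as it is.

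- **The confirmatory result is protected.** The primary endpoint is measured before unblinding is allowed, and no confirmatory claim rests on month 12. This stands, and it limits the weight of the point. Exploratory status lowers what is claimed from a result, but it does not remove measurement bias.
- **The limit is disclosed.** The three statements of it agree, so this is an open design choice and not a contradiction. This stands too.
- **Masking the side helps.** KT-1000 laxity is the repaired-minus-healthy difference. An examiner who knows the device but not the operated knee has less scope to push that difference in a chosen direction. This stands if the dressings work, but a patient may reveal the side, and the device would still be known.
- **The figures rest on assumptions.** The calculation needs a uniform shift, and therefore general unblinding. It also needs 24 evaluable per arm at 12 months, and a 12-month t-test that the article does not specify. This stands; the table is an illustration and not an estimate.

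A reader might also infer more than the document supports:

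- *That the 12-month data are unblinded.* The wording permits disclosure and does not schedule it.
- *That the trial's main question is compromised because it concerns long-term stability.* The Discussion does say that "it is unclear whether screw or pins lead to better long-term stability", but as an argument for equipoise. The tested hypothesis is fixed at six months.
- *That the planned modelling is contaminated.* Statistical analysis mentions models for correlated data only as something to consider, and names none that uses month 12.
- *That blinding examiners would protect every 12-month outcome.* Patient-reported scores depend on what the patient knows.

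**Conclusion.** The point holds in limited form. The protocol permits examiners to learn the allocation before they repeat examiner-dependent laxity tests at the only later visit, and it states no reason. The exploratory 12-month laxity data are therefore open to unblinded assessment. The six-month primary comparison, its error rate and its power are untouched.

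The size of any bias is unknown. Under the assumptions in the working, a shift of 0.1 mm would hardly matter (about 6% nominal significance against 5%), while 0.3 mm and 0.5 mm would give about 14% and 29%. Effective side masking, or disclosure to only some examiners, would make the effect smaller. The change is still worth making because it is cheap, and blinding once lost cannot be restored.

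**What to change.** Amend two places, the Abstract (Design/Methods) and the closing statement under Six months postoperatively, so that:

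1. patients may be told their allocation after the six-month CRF, as now;
2. the independent follow-up examiners stay blinded until the last patient's 12-month CRF is closed;
3. patients who have been told are asked not to disclose the device to the examiners.

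State that the dressings are also used at 12 months, and report 12-month patient-reported scores as open-label.

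The statement to patients under Ethical considerations can stand, because the timing of their own disclosure does not change. Alpha, power, sample size, visits, staff and procedures are unaffected. The downsides are small: examiners learn the allocation later, and some patients may still reveal it, so the change reduces the risk of bias but does not eliminate it.
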